### Study objectives – primary and secondary endpoints

The trial includes four co-primary endpoints to assess the efficacy of the proposed strategy to inhibit or attenuate the subclinical manifestations of anthracycline-induced cardiotoxicity (AIC). The co-primary endpoints include two imaging variables, a serum biomarker and electrocardiographic variables. The first co-primary endpoint is changes in LVEF from baseline control to 180 days after the first chemotherapy cycle, determined by CMR. The second co-primary endpoint is the percentage of changes in global longitudinal strain (GLS) comparing baseline with 90 and 180 days after the first cycle, determined by two-dimensional ECHO. The third co-primary endpoint is the elevation in serum biomarkers, including NT-ProBNP between baseline and 48 h after the first chemotherapy cycle and/or elevations in levels of hs-cTnT at 2, 4 and 90 days. The fourth co-primary endpoint is the prolongation in the corrected QT interval, 48 h after the first chemotherapy cycle.

Additionally, three secondary endpoints were included to determine other imaging and clinical variables, as well as to evaluate systemic biomarkers of oxidative stress. The first secondary endpoint is the occurrence of major adverse cardiac events during follow-up such as: cardiac death, acute coronary syndrome, acute pulmonary edema, clinical manifestations of heart failure and life-threatening arrhythmias. The second secondary endpoint is changes in LVEF from baseline compared to 90 and 180 days after the first chemotherapy cycle, determined by two-dimensional ECHO. The third secondary endpoints are biomarkers of oxidative stress damage, as well as parameters of intracellular and extracellular antioxidant balance. In order to evaluate the oxidative stress damage, plasma lipoperoxidation levels (malondialdehyde levels) will be measured at 2, 4 and 180 days after the initial chemotherapy cycle. To evaluate antioxidant balance, the Erythrocyte Thiol Index (GSH/GSSG) will be determined at 2, 4 and 90 days after the first chemotherapy cycle. Given this is a pilot study, outcomes will include the total number of patients screened, those eligible, those providing informed consent and those completing the intervention treatment.

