### Sample size and data analysis

The sample size was estimated on the basis of results from our previous protocol (63), where the carvedilol-supplemented group showed a 51% reduction of differential LVEF (ΔLVEF) compared with the placebo group. ΔLVEF was determined between the last follow-up ECHO at approximately 1 year (10–12 months) with respect to baseline ECHO, both performed by two-dimensional evaluation. Assuming normal distribution and a common relative standard deviation of 48% (supplemented group), with 5% two-sided significance, a sample size of 32 will be required to provide 80% statistical power to detect a 12.5% ΔLVEF reduction assessed by CMR to provide greater precision.

Results will be analyzed according to intention-to-treat criteria, including all randomized patients who are able to initiate intervention, independent of treatment and follow-up period durations. Continuous variables will be expressed as means ± standard deviation or medians and interquartile ranges depending on their distribution. Distribution will be analyzed using the Kolmogorov-Smirnov test. Student’s *T* test and Pearson correlation analyses will be applied for normally distributed continuous variables. The Mann-Whitney *U* test and Spearman’s correlation will be used for non-normally distributed continuous variables. Categorical variables will be expressed as numbers and frequencies (%). Differences between the frequencies will be performed by the chi-square test or by Fisher’s exact test. Multiple linear regression analysis will be used to assess independent predictors of the absolute semiannual changes in ΔLVEF, to identify factors associated with ΔLVEF. The difference between the groups will be considered significant with a *p* value of < 0.05.

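### The arms are compared by unadjusted tests on change or percent change although baseline values are collected; adjusting for baseline would usually be more precise, by an amount the article does not allow one to fix

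*Protocol article*

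**What the plan says.** Under Study objectives, two of the four co-primary endpoints are explicit change measures:

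- LVEF: "The first co-primary endpoint is changes in LVEF from baseline control to 180 days after the first chemotherapy cycle, determined by CMR".
- GLS: "the percentage of changes in global longitudinal strain (GLS) comparing baseline with 90 and 180 days after the first cycle", by two-dimensional echocardiography.

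The other two are rises in NT-ProBNP and hs-cTnT and prolongation of QTc, also measured from a starting value.

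Under Enrollment and baseline phase assessments, the biomarkers, electrocardiogram, echocardiogram and CMR are all obtained at least 10 days before the first cycle and before allocation. Each endpoint therefore has its own pre-treatment value.

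Under Sample size and data analysis, a Kolmogorov-Smirnov test decides between two unadjusted comparisons. Student's T "test and Pearson correlation analyses will be applied for normally distributed continuous variables"; Mann-Whitney is used for the rest. The only model named serves another purpose: "Multiple linear regression analysis will be used to assess independent predictors of the absolute semiannual changes in ΔLVEF". It is not described as the comparison of the arms. Its wording is also loose, because the same section determines ΔLVEF as follow-up relative to baseline, so a change in ΔLVEF is a change of a change.

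**The concern.** A simple change score subtracts the whole baseline value, which fixes the slope of follow-up on baseline at 1. With equal SDs at the two visits the true slope is r, which is below 1, so the subtraction over-corrects. This has two consequences.

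- The treatment estimate is noisier than the collected data allow.
- When the arms happen to differ at baseline, the estimate is shifted in a known direction by regression to the mean.

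Percent change has the same difficulty and also divides by a noisy baseline. The described randomization uses blocks of four and mentions no stratification, so nothing in it balances baseline LVEF or GLS. The article itself lists small sample size as a main limitation and turns to CMR for precision. Giving some of that precision back in the analysis works against its own aim.

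**Working it through.** **Inputs from the article.** N = 32, 1:1, hence 16 per arm; 5% two-sided; 80% power; detectable effect 12.5%; relative SD 48%; pilot effect 51%.

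**Inputs assumed.** The correlation r and the ratio k of follow-up SD to baseline SD. Neither is in the article, so ranges are shown.

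**1. The plan's own figure.** The plan gives 32 patients in all as enough "to provide 80% statistical power to detect a 12.5% ΔLVEF reduction assessed by CMR". Taking 12.5% and 48% on one scale, n per arm = 2(1.960 + 0.842)²(48/12.5)² = 231.5, so 232 per arm and 464 in total; 16 per arm gives about 11% power. With the pilot's 51%, the same formula gives 2(1.960 + 0.842)²(48/51)² = 13.9, so 28 in total (30 by the t distribution). Thus 32 roughly fits a 51% effect, not 12.5%. That mismatch is a separate matter. It matters here only because it leaves no agreed starting power to improve on. The relative gain below does not depend on it.

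**2. Relative precision for LVEF, equal SDs.** With common SD σ:

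- Var(change) = 2σ²(1 − r)
- Var(ANCOVA) = σ²(1 − r²)
- Ratio = (1 + r)/2, so equivalent N = 32 ÷ [(1 + r)/2]

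Estimating the slope multiplies the ANCOVA variance by about 1 + 1/(N − 4) = 1 + 1/28 = 1.036.

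| r | Variance ratio | Equivalent N | Gain, large sample | Gain after slope cost |
|---|---|---|---|---|
| 0.3 | 0.65 | 49.2 | 17.2 | 15.5 |
| 0.5 | 0.75 | 42.7 | 10.7 | 9.2 |
| 0.7 | 0.85 | 37.6 | 5.6 | 4.4 |
| 0.8 | 0.90 | 35.6 | 3.6 | 2.3 |
| 0.9 | 0.95 | 33.7 | 1.7 | 0.5 |

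A simulation at 16 per arm (assumed LVEF mean 62, SD 5) agrees: gains of about 9.7 at r = 0.5, 3.9 at 0.7 and 0.4 at 0.9.

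**3. Unequal SDs.** In general, in units of the baseline variance, Var(change) = 1 + k² − 2rk and Var(ANCOVA) = k²(1 − r²). Large-sample gains:

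- k = 1.25: 3.8 patients at r = 0.5, 0.6 at r = 0.7. At r = 0.8, 1 + 1.5625 − 2 = 0.5625 and 1.5625 × 0.36 = 0.5625, so the gain is zero. After the slope cost it is a loss of about one patient (32/1.036 = 30.9).
- k = 0.8: 24 patients at r = 0.5, 19 at r = 0.7.

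**4. Conditional bias, equal SDs.** The chance baseline difference between arms has SD σ√(2/16) = 0.35σ, and a gap at least that large occurs in about one trial in three. The change-score contrast is then off by (1 − r) × gap. The standard error of that contrast is σ√[2(1 − r)] × √(2/16).

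- r = 0.5: shift 0.18σ, standard error 0.35σ, so about half a standard error.
- r = 0.7: shift 0.11σ, standard error 0.27σ, so about 0.4 of a standard error.

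**5. GLS.** (1 + r)/2 does not apply directly to percent change. A simulation at 16 per arm with assumed mean 20 and SD 2.5, equal at both visits, gave gains over percent change of about 11.8 patients at r = 0.5, 6.5 at 0.7 and 1.9 at 0.9. Over simple change in GLS the first two were 8.7 and 4.2. These figures only illustrate the direction.

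**The case against.** The strongest reply is that nothing here is an error. Under 1:1 randomization a t test on change is valid and, averaged over randomizations, unbiased. The analysis section is a general list by variable type, and covariate adjustment is often left to an analysis plan. The validity point stands in full: a reader might infer that the planned comparison is invalid or biased, and the article does not support that. The bias in step 4 is conditional on a chance imbalance. The second point carries less weight, because the article does not leave the method open. It names the tests and gives its one regression to another task.

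A second reply concerns size, and it stands. A reader might infer a firm gain of roughly 6 to 11 patients. That is only the large-sample result for r between 0.5 and 0.7 with equal SDs; the article gives no r. Equal SDs may also fail: baseline LVEF below 50% is excluded, which truncates the baseline, and response to a cardiotoxic exposure may widen the follow-up distribution. A larger follow-up SD is plausible, though not shown.

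A reader might likewise infer a rise in power from 80% to between 86% and 90%. That presumes 80% to begin with, which the stated 12.5% effect with 48% SD does not deliver at 16 per arm.

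Finally, GLS percent change is a declared endpoint, and 30 patients were enrolled by October 2018. That is a reason to retain it as a reported quantity. It is not a reason to leave the arm comparison unadjusted.

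**Conclusion.** The point holds as a loss of precision that can be avoided, together with a conditional bias under chance baseline imbalance. It is not a fault of validity. For LVEF, with equal SDs, the gain ranges from about 17 patients at r = 0.3 to 2 at r = 0.9 in large samples, or about 15.5 to 0.5 once the slope is paid for. It can be zero or slightly negative when the follow-up SD exceeds the baseline SD, and larger when it is smaller. For GLS only the direction is supported, and no absolute power can be claimed for any endpoint. The change should be made because it is nearly free and the trial is small, not because a particular number of patients is known to be at stake.

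**What to change.** - For each continuous co-primary endpoint, make the arm comparison an ANCOVA of the follow-up value on arm and the same measure's baseline: CMR LVEF, GLS in its own units, QTc, and NT-ProBNP and hs-cTnT on the log scale because they are skewed. For LVEF this gives the same treatment effect as change adjusted for baseline, so the declared endpoint is kept.
- Report the adjusted difference with its 95% confidence interval (a ratio for the logged biomarkers).
- Where an endpoint has several time points, fit the model at each declared one.
- Keep the unadjusted t or Mann-Whitney test as a sensitivity analysis, and report the declared percent change in GLS as a sensitivity or descriptive result.
- Label the predictor regression exploratory, and reword its outcome as ΔLVEF rather than a change in ΔLVEF.

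The cost is one degree of freedom per model and a small loss of precision if r is very high. No new data are needed. The article describes follow-up as ongoing and analysts as blinded; the change should be written down and dated before unblinding.

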## Discussion

CarDHA is a limited, academic, randomized, placebo-controlled, double-blind, two-arm clinical trial designed to evaluate the efficacy of the proposed strategy to inhibit or attenuate subclinical manifestations of anthracycline-induced cardiotoxicity (AIC).

The four co-primary endpoints of the study are: (1) changes in LVEF as evidenced by CMR; (2) changes in global longitudinal strain (GLS) manifested in echocardiographic imaging; (3) elevations in levels of serum biomarkers (NT-ProBNP/hs-cTnT); and (4) QT interval prolongation by electrocardiographic evaluation.

Unlike similar AIC primary prevention protocols based on carvedilol alone, to our knowledge this trial is the first cardio-oncology study to: (1) be expressly designed as a therapeutic strategy focusing on attenuating the oxidative stress associated to AIC, rather than on the β-blocking effects of carvedilol; and (2) attempt to evaluate the potential cardioprotective effects of a dual strategy (comprising non-ischemic cardiac preconditioning through endogenous antioxidant capacity enhancement through DHA, plus the direct antioxidant properties of carvedilol, in a sequential regimen specifically designed to attenuate chemotherapy-induced oxidative stress). We expect the inhibition or attenuation of the anthracycline-derived oxidative heart injury generated by two unrelated antioxidant pathways will be more efficient than the potential of one the pathways alone.

The main limitations of our study are the small sample size, the non-use of consensus criterion (post-chemotherapy LVEF decline ≥ 10% to < 50%) to define a cardiotoxic event for the first co-primary endpoint [6] and to have a single-center trial. The use of CMR imaging to evaluate our first co-primary endpoints, the gold-standard method to evaluate LVEF decline, partially compensates the first two limitations, since we are not limited by echocardiographic sensitivity and should be able to detect subclinical cardiotoxicity at the early stages [10]. Additionally, although most cardio-oncology trials have used the ≥ 10% consensus criterion to establish cardiotoxicity, that range was defined arbitrarily as a criterion for two reasons: first, it is widely used as cut-off point to evaluate the continuity of oncological treatment; and second, it reflects the echocardiographic sensitivity limits to establish a decline in LVEF with certainty [10]. A smaller than 10% in AIC-induced LVEF reduction does not imply the absence of cardiotoxicity. Thus, other clinical trials with relatively small sample sizes using CMR to evaluate LVSD as the primary endpoint, such as the PRADA and MANTICORE trials, also rule out the criterion of a LVEF decline ≥ 10% for event definition, in favor of comparing mean differences between the groups [61, 62]. Moreover, limiting the description of a cardiotoxic event to a consensus definition of decline in LVEF can underestimate the manifestation of other types of cardiotoxicity (such as an elevation in cardiac biomarkers), some of which could be associated with the future development of later clinical manifestations [63, 64]. Regarding the lack of representativeness associated with single-center studies, the San Juan de Dios is a public hospital that provide healthcare to a large urban population, and several rural surrounding locations. It also has the advantage that all echocardiographic images will be performed by the same person, and analyzed by the same two specialist. Additionally, it plays in our favor the fact that in Chile the doxorubicin protocol for localized breast cancer is standardized in all public hospitals and is quite similar among private health services.

The relative short follow-up time (6 months) could also be considered a problem in this study. Nevertheless, Cardinale et al. previously reported in a large prospective study, including 2625 patients, an early LVEF drop in patients developing cardiotoxicity [6]. In that study the median time elapsed between the end of chemotherapy and cardiotoxicity development was 3.5 months. Therefore, it sems to be difficult not to find differences at 6 months through CMR. Finally, for some authors, the use of a combination therapy could also be considered a limitation [35]. This implies a difficulty when comparing our results to similar studies based on carvedilol alone. Our design also difficult estimating attributable fraction to carvedilol if we find beneficial effects. Notwithstanding, we maintain that beyond the use of CMR, the greatest contribution of this protocol is to evaluate a prophylactic strategy completely designed to attenuate the oxidative stress derived from AIC, with the inclusion of two different antioxidant strategies administered sequentially to enhance the effects.

In conclusion, CarDHA is the first randomized trial designed to evaluate the potential cardioprotective effects of a dual antioxidant strategy comprising a non-ischemic pharmacologic cardiac preconditioning based on DHA and carvedilol, specifically designed to attenuate oxidative stress as a key factor in AIC development and progression. Potentially favorable results of this study will generate the basis for larger clinical trials to further explore the efficacy of this innovative strategy.

## Trial status

The protocol was reviewed and approved by the Institutional Review Board of the San Juan de Dios Hospital and the Ethics Committee of the University of Chile, whose medical school is associated with San Juan de Dios Hospital, as only the university has a committee accredited by the Chilean Ministry of Health.

Enrollment was started on 30 May 2016. However, the first patient entered into the study on 10 August 2016. As of 26 October 2018, the study had enrolled 30 patients at the San Juan de Dios Hospital. The study is being conducted in accordance with “Good Clinical Practice” recommendations, based on the Declaration of Helsinki (2002). The trial has been registered at the ISRCTN registry with the code ISRCTN69560410 applied on 8 June 2016. A flow chart of this study is presented in Fig. 3.

**Fig. 3 Fig3:**
[figure not shown]
Flow chart of the Carvedilol-DHA (CarDHA) trial

## Data Availability

The datasets generated and/or analyzed during the current study are available from the corresponding author on reasonable request.

## Abbreviations

AIC: Anthracycline-induced cardiotoxicity
CarDHA: Carvedilol-DHA trial
CMR: Cardiac magnetic resonance
DHA: Docosahexaenoic acid
ECHO: Echocardiography
GLS: Global longitudinal strain
HF: Heart failure
hs-cTnT: High-sensitivity cardiac troponin T
LVEF: Left ventricular ejection fraction
LVSD: Left ventricular systolic dysfunction
NT-ProBNP: NT-proB-type natriuretic peptide
ROS: Reactive oxygen species
TnI: Troponin I
Top2β: Topoisomerase 2 Beta
ΔLVEF: Differential LVEF
